# Experimental Design:

# This will be a two-arm randomized study comparing a placebo control arm to supplementation with a commercial soy supplement. The time of initial biopsy to the time the surgery scheduled is typically 2-4 weeks in normal setting. Patients will be treated for a minimum of two weeks and continue treatment until the time of their prostatectomy. A total of 86 patients will be randomized (43 patients/arm).

Supplementation with Soy Isoflavones:

Dose Levels:

Dose 0: No soy (Placebo).

Dose 1: Four Capsules Twice Daily (240 mg of total isoflavones).

Treatment: The commercial soy supplement to be used is *Flav-Ein* (3B’s LTD, Lexena, Kansas)*.* This product was chosen because it is a pure soy extract and the individual concentration of each soy isoflavone is closely equivalent to a soy-based diet. It is supplied in capsular form. Each capsule contains 560 mg of pure soybean extract and 100mg of a non-soy legume (see appendix). Each capsule contains approximately 30mg of total isoflavones. The placebo will consist of an equivalent capsule with only the 100mg legume additive and no soy supplement.

1. ELIGIBILITY/EXCLUSION CRITERIA:

All patients must meet the following eligibility and exclusion criteria:

1. Histologically proven adenocarcinoma of the prostate.
2. Surgical candidate for radical prostatectomy.
3. During time of study period, patients must agree not to take any new vitamin supplementation or herbal remedy.
4. Must not be receiving concurrent chemotherapy, radiation or hormonal therapy.
5. No history of prior allergy and intolerability to soy-based products.
6. Must not have been taking any soy supplementation or soy isoflavones within 90 days prior to study enrollment.
7. Must be able to safely be on replacement for period of at least two weeks prior to the scheduled prostatectomy.
8. All patients must have been informed of the investigational natures of this study and must sign and give written informed consent in accordance with institutional and federal guidelines.
9. **STUDY CALENDAR**

| REQUIRED  STUDIES | Study Enrollment | Two Weeks | Preprostatectomy |
| --- | --- | --- | --- |
|  |  |  |  |
| EXAM |  |  |  |
| History/PE | X | X | X |
| Weight | X | X | X |
| PS | X | X | X |
| Toxicity | X | X | X |
|  |  |  |  |
| SERUM# |  |  |  |
| PSA | X | X | X |
| Estrogen(total) | X | X | X |
| Estradiol | X | X | X |
| Testosterone | X | X | X |
| DHT | X | X | X |
| SHBG | X | X | X |
| IGF-1 | X | X |  |

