1. CRITERIA FOR REMOVAL FROM STUDY
2. Progression of disease.
3. Resultant delay of surgery treatment greater than 3 weeks.
4. Unacceptable toxicity: there will be no dose reductions, any patient with unacceptable toxicity will be removed and proceed with planned prostatectomy.
5. The patient may withdraw from the study at any time for any reason.

1. HUMAN SUBJECTS:
2. **Risk of Subjects**

Human Subject Involvement and Characteristics: This study will involve patients who are scheduled to undergo radical prostatectomy for treatment of their prostate cancer. Patient will receive variable doses of a soy supplement from the time of study enrollment until the time of their planned surgery. All patients must have histologic confirmation of adenocarcinoma of the prostate must be surgical candidates as dictated by their disease stage and health status. Because of disease being studied, all patients will be males of all ethnic backgrounds who are greater than 18 years of age with the expected age range of 55-70. All patients must meet the following additional eligibility and exclusion criteria: a) patients must agree not to take any new vitamin supplementation or herbal remedy, b) must not be receiving concurrent chemotherapy, radiation or hormonal therapy, c) no history of prior allergy and intolerability to soy-based products, d) must not have been taking any soy supplementation or soy isoflavones within 90 days prior to study enrollment, e) must be able to safely be on supplements for period of at least two weeks prior to the scheduled prostatectomy, f) all patients must have been informed of the investigational natures of this study and must sign and give written informed consent in accordance with institutional and federal guidelines. A total of 86 patient will be accrued over a three-year period.

Sources of Materials: Sources of research material include serum, tissue specimens and clinical data which will include toxicity data and demographic characteristics. Serum will be collected at study enrollment, after two weeks, and at the time of prostatectomy. Prostate tissue will be collected at the time of the diagnostic biopsy and prostatectomy. All material will be collected specifically for research purposes.

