Potential Risks: Although there was no toxicity seen in the pilot trial, the potential research risk of treating with an estrogenic agent includes an increase risk of thrombosis, gynecomastia, fluid retention and elevation of liver function tests. Based on preliminary data and prior studies, these risks are of low likelihood and readily reversible with the exception of thrombosis. Although it is of low likelihood, thrombosis can lead to fatal pulmonary embolism in a small percentage of case. Phlebotomy risks include pain at the injection site and infection. There are no known social, psychological and legal risks. Therapeutic risks include postoperative thrombosis, infection, impotency and incontinence which all can occur with a standard prostatectomy**.** The thrombotic risk is expected to be extremely with no risk reported in other published trials of soy supplementations.

1. **Adequacy of Protection for Risks**

Recruitment and Informed Consent: Potential patients will subjects who have been referred to the urology clinics at the VAMC for evaluation of a potential prostate cancer (elevated PSA, DRE) and have subsequent documentation of an invasive prostate cancer. Only patients who are surgical candidates and have chosen surgical as their treatment choice will be offered participation. Patient will be provided consent form, information on soy supplementation and study aims in lay language. Potential candidates will be identified by participating investigators ([name], [name], [name]) who will also answer questions and provide additional education on the study. Patients will be allowed to read and take the consent home. Final consent will be obtained by [name] (Research Associate). Copy of the informed consent will be submitted to the IRB and maintained in the patient record. The IRB the Kansas City VAMC has not authorized a modification or waiver of the elements of consent or its documentation. All clinical personal have had human subjects/informed consent training.

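### Thrombosis is named as a possibly fatal risk of the supplement, yet neither eligibility list excludes men with a previous deep vein thrombosis or pulmonary embolism

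*Protocol*

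**What the plan says.** The Introduction lists thrombosis among the potential estrogenic effects of soy. Human Subjects, Potential Risks, repeats it as a risk of treating with an estrogenic agent. It says that "these risks are of low likelihood and readily reversible with the exception of thrombosis", and then: "Although it is of low likelihood, thrombosis can lead to fatal pulmonary embolism in a small percentage of case". The same paragraph expects the thrombotic risk to be very small, with "no risk reported in other published trials of soy supplementations", and counts clotting among the hazards of the operation itself: "Therapeutic risks include postoperative thrombosis".

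On exposure, Experimental Design says: "Patients will be treated for a minimum of two weeks and continue treatment until the time of their prostatectomy". The interval is short: "The time of initial biopsy to the time the surgery scheduled is typically 2-4 weeks in normal setting".

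The Eligibility/Exclusion Criteria have eight items. The closest to this hazard is item 7: "Must be able to safely be on replacement for period of at least two weeks prior to the scheduled prostatectomy". The Human Subjects list (items a to f) has the counterpart at item e: "must be able to safely be on supplements for period of at least two weeks prior to the scheduled prostatectomy". Neither list mentions previous deep vein thrombosis, pulmonary embolism, thrombophilia or anticoagulation.

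Under Protection Against Risk, a man who develops a thrombosis leaves the study and is anticoagulated.

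**The concern.** The protocol names a hazard, says it can kill, and gives it its own rule after an event, but sets no rule for it before enrollment. It does screen by history for another hazard: soy allergy or intolerance is an exclusion in both lists. A previous clot, the obvious marker for the graver hazard, is not.

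A man with a previous clot whom the investigator judges able to take the supplement safely meets every listed criterion. He then has a 1 in 2 chance of taking the active supplement until surgery. The operation carries its own clot risk whether or not he enrolls, and the documents do not show that soy adds to it. But the Risk/Benefit paragraph rates direct benefit to participants as low, so even a small avoidable risk has little to offset it. That a previous clot marks higher risk is ordinary clinical knowledge; the protocol does not state it.

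**Working it through.** **Text check.** The protocol states no figure on this point, so the check begins with its sections side by side.

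| Question | What the protocol provides |
|---|---|
| Is thrombosis named as a supplement risk? | Yes: Introduction; Human Subjects, Potential Risks |
| Is it treated as the gravest listed supplement risk? | Yes: the one exception on reversibility, and possibly fatal |
| Does Eligibility/Exclusion Criteria, items 1-8, exclude a clot history? | No |
| Does Human Subjects, items a-f, exclude a clot history? | No |
| Is there a general item that could cover it? | Item 7 / item e, and surgical candidacy; neither names a condition |
| What acts after enrollment? | History and examination at two weeks and before surgery; toxicity checks at those times and after surgery; stopping for grade 3 or 4 events; safety board oversight; six-monthly toxicity review; removal and anticoagulation after a clot |

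The post-enrollment measures are real, but they monitor or respond. Only the eligibility criteria can keep a higher-risk man out.

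**Size.** The documents give neither a thrombosis rate nor a prevalence of previous clots, so harm avoided cannot be computed. What can be shown is how many men the exclusion would touch, for an assumed prevalence p of previous deep vein thrombosis, pulmonary embolism or known thrombophilia. The working assumption is p = 3-8%; lower values are shown for sensitivity.

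Inputs from the protocol: 86 men, 43 per arm (Experimental Design); three-year accrual (Human Subjects); 40-50 prostatectomies a year (Patient Accrual), so 3 × 40 = 120 to 3 × 50 = 150.

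Formulas:
- Men affected = 86p; on soy = 43p.
- Chance of at least one on soy = 1 − (1 − p)^43.
- Candidates lost = 120p to 150p.
- Accrual time = 36/(1 − p) months, if candidates limit accrual and uptake is unchanged.

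| p (assumed) | Of 86 | Of 43 on soy | At least one on soy | Lost of 120-150 | Accrual, months |
|---|---|---|---|---|---|
| 1% | 0.9 | 0.4 | 35% | 1.2-1.5 | 36.4 |
| 3% | 2.6 | 1.3 | 73% | 3.6-4.5 | 37.1 |
| 5% | 4.3 | 2.2 | 89% | 6.0-7.5 | 37.9 |
| 8% | 6.9 | 3.4 | 97% | 9.6-12.0 | 39.1 |

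Over 3-8%, that is about 3-7 men enrolled, 1-3 on soy, 4-12 candidates lost, and 1.1-3.1 extra months. The delay is an upper limit at each p, because item 7 may already exclude some of these men.

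**Can accrual bear it?** Required uptake now is 86/150 = 57% to 86/120 = 72%. In the worst case it becomes 86/(120 × 0.92) = 86/110.4 = 78%. Patient Accrual reports pilot acceptance close to 100%.

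**The case against.** The strongest reply is that the hazard is already covered and is probably negligible. Item e asks whether a man can safely be on the supplement, so an investigator who thinks a previous clot makes it unsafe must exclude him. The calendar schedules a history and examination at enrollment, where that judgement can be made. Reading the item as asking only whether surgery can wait two weeks is possible but not the most natural reading, since delay of surgery has its own removal rule.

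The expected risk is also very low. The Introduction puts isoflavones at 1/1,000 to 1/100,000 of the activity of synthetic estrogens and reports no significant toxicity at comparable doses. The pilot saw no toxicity, exposure is a few weeks, and the quoted genistein half-life of 3-6 hours limits carry-over past surgery. The prevalence range has no source in the documents, and a lifetime exclusion also removes men whose clot was long ago.

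Much of this stands. It is why no harm is quantified and why the point ranks as an optional improvement. Two things remain. The general item names no condition, so two investigators could decide differently about the same man. And the pilot reassures only weakly: it enrolled 13 men, and even if all took soy, zero events gives a one-sided 95% upper limit of 1 − 0.05^(1/13), about 21%. The consent form is not shown and may warn such men, but a warning is not an eligibility rule.

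**Conclusion.** The point holds, as a low-cost safety improvement. The protocol identifies a possibly fatal risk of the supplement, rates direct benefit to participants as low, and leaves men with previous clots to a general judgement. Eligibility is fixed in the protocol, so this is not a matter for a later analysis plan.

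The number of men concerned is small and rests on an assumed prevalence: about 3-7 of 86 at 3-8%, and fewer than one at 1%. These are counts of men with a history, not of clots. The documents do not show that the supplement raises clot risk in such men. Confidence is medium, because the omission is plain from the text while its practical consequence is not known.

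**What to change.** Add one item to both lists (Eligibility/Exclusion Criteria, and Human Subject Involvement and Characteristics): *No history of deep vein thrombosis or pulmonary embolism, and no known thrombophilia (a disorder that increases clotting).* Check it by history at the enrollment visit already in the Study Calendar. No laboratory screening is needed.

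The cost is one line in two places, with no new test or visit. The real price is the loss of some candidates, including men with remote clots, and the modest accrual delay worked out above. If the sponsor prefers to keep men with remote clots eligible, a weaker alternative is to have the investigator record, under item 7 and item e, that clot history was considered and why the supplement is judged safe.
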